#### Statistical analysis and power calculation

Analyses will start once baseline data has been collected and cleaned. Descriptive statistics will be produced for all outcome measures, and outcome trajectories from t_0_ to t_3_ will be examined via exploratory analyses. The intervention’s effect on primary and secondary outcomes will be tested by means of random-effect regression models including a fixed group effect over time, allowing the inclusion of cases with incomplete (unbalanced) data across panels [36]. Post-hoc analyses will examine early (at t_1_) and late (at t_3_) effects for primary and secondary outcomes. All outcome analyses will be performed on an intention-to-treat basis. Per-protocol analyses will be part of the process evaluation (see below).

Sample size calculation was performed for testing whether the primary outcome (social inclusion) at t_2_ is affected by allocation. For six study sites, three time points, and estimated panel attrition of 10% at each time point, *N* = 558 participants (*N* = 93 per site) will be needed to detect a small effect size (0.25 SD units) with a power of 0.80 at a two-tailed significance level of 0.05. Sample size calculation was performed using the RMASS program (www.rmass.org) for a three-level mixed-effects linear regression model for the analysis of longitudinal data, assuming a linear effect over time, compound symmetry for error variance covariance, a person-level covariance (Int, Cov, Slope) of 0.300, 0.150, 0.100, and a centre-level covariance (Int, Cov, Slope) of 0.050, 0.025, 0.020.

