
##### Outcomes

The primary outcome is social inclusion at t_2_ (8 months). This time point has been chosen because it is shortly after the intervention has been completed, but also allows time for changes in social inclusion to take place. Social inclusion is a key outcome in global mental health [29] and will be measured with the Social Inclusion Scale (SIS [30]) which is a service-user-reported measure with 16 items answered on a four-point Likert scale (“not at all”; “not particularly”; “yes a bit”; “yes definitely”). The total SIS score consists of the prorated sum over the 16 items, and can range from 16 to 64, with higher scores representing higher levels of social inclusion. The SIS has previously been shown to have adequate psychometric properties [30] which will be further investigated for the different language versions used in this trial.

Secondary outcomes are empowerment (using the Empowerment Scale, ES [31]), hope (using the HOPE scale [32]), recovery (using the Stages of Recovery, STORI-30 [33]), and health and social functioning (using the Health of the Nations Outcome Scales, HoNOS [34]). Established state-of-the-art translation guidelines [35] will be followed to translate and locally validate the standardised measures (including administration instructions) to be used, with special attention paid to the psychometric evaluation of the primary outcome. See Puschner et al. [13] for further details on translation.

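### The primary outcome is SIS at 8 months, but the named test is an unspecified group effect over time; the t2 arm difference is never made the primary test

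*Protocol article*

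**What the plan says.** The Outcomes section of the protocol article ties the primary outcome to one visit: "The primary outcome is social inclusion at t_2_ (8 months". The section on statistical analysis and power agrees on the question: "Sample size calculation was performed for testing whether the primary outcome (social inclusion) at t_2_ is affected by allocation". It also sets the other follow-up visits apart: "Post-hoc analyses will examine early (at t_1_) and late (at t_3_) effects for primary and secondary outcomes".

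The test itself is described only as "random-effect regression models including a fixed group effect over time". The section does not say:
- whether the primary result is the arm difference at t2, a slope difference, or an effect pooled over visits;
- whether t0 to t2 or t0 to t3 enter the model;
- how baseline SIS is handled.

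The sample size comes from a three-level linear mixed model with three time points, "assuming a linear effect over time". The trial has four measurement points. The Intervention section says that peer support lasts at most 6 months, so it ends before t2 and about half a year before t3.

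**The concern.** An arm difference at month 8 and a group effect over time are different quantities. They agree when the effect grows in proportion to time over the visits in the model. With support ending by month 6, steady growth to month 12 is doubtful: the effect may level off or fade.

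Two things are at stake. First, if a linear group-by-time term is fitted to all four visits, the t3 data pull the line away from the 8-month effect, and a real effect at t2 can be understated or missed. Second, the current wording permits several tests that can give different answers, and the choice among them should be fixed before the allocation is known. A smaller matter is that baseline SIS is already collected and could add precision, but its use is not stated.

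**Working it through.** **Inputs from the protocol (Statistical analysis and power calculation; Allocation).** N = 558, allocated 1:1 within six sites; effect 0.25 SD; "with a power of 0.80" "at a two-tailed significance level of 0.05"; attrition of 10% per time point, so retention is 1, 0.90, 0.81 (and 0.729 at t3). Person-level covariance (intercept, covariance, slope) is 0.300, 0.150, 0.100; centre-level is 0.050, 0.025, 0.020.

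**Assumptions.** The error variance is not given; I take 1 and also show 0.5 and 0.25. Errors are independent given the random effects, visits are coded 0, 1, 2, 3, and the 0.25 SD is scaled to the SD at t2. Because allocation is balanced within site, centre effects cancel from the arm contrast.

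**Step 1, target effect.** Variance at t2 = 1 + (0.300 + 2×2×0.150 + 4×0.100) + (0.050 + 2×2×0.025 + 4×0.020) = 1 + 1.300 + 0.230 = 2.530. SD = 1.591, so d = 0.25 × 1.591 = 0.398.

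**Step 2, the plan's N.** I used the generalised-least-squares information with V = ZGZ' + σ²I, summed over the monotone dropout patterns. The tested term is the group-by-time slope over t0 to t2, with the baseline arm difference free. N = Var × (1.960 + 0.842)² / d² = 560, against 558 stated. At N = 558, d/SE = 0.398/0.142 = 2.80 and power is Φ(2.80 − 1.96) = 0.80.

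This match does not identify the model. The same model gives 411 at error variance 0.5 and 300 at 0.25. A plain two-sample calculation (252 per arm, 504 in total) divided by 0.90 also gives 560.

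**Step 3, what a line reports when the true t2 effect is 0.25 SD.** The estimate is twice the slope difference, with free baseline. Power is Φ(k·d/SE − 1.96), where k is the estimate as a share of the truth. For four visits d/SE = 3.81; for three it is 2.80.

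| Visits fitted | True effect at t0, t1, t2(, t3), as share of t2 effect | k | Estimate (SD) | Power of line |
|---|---|---|---|---|
| t0–t3 | 0, 0.5, 1, 1.5 (keeps growing) | 1.00 | 0.25 | 0.97 |
| t0–t3 | 0, 0.5, 1, 1 (plateau after t2) | 0.72 | 0.18 | 0.79 |
| t0–t3 | 0, 0.5, 1, 0.5 (halves by t3) | 0.45 | 0.11 | 0.40 |
| t0–t3 | 0, 1, 1, 1 (full effect from t1) | 0.65 | 0.16 | 0.70 |
| t0–t3 | 0, 1, 1, 0.5 (full from t1, halves by t3) | 0.37 | 0.09 | 0.30 |
| t0–t2 | 0, 0.5, 1 | 1.00 | 0.25 | 0.80 |
| t0–t2 | 0, 1, 1 | 1.04 | 0.26 | 0.83 |
| t0–t2 | 0, 0, 1 | 0.96 | 0.24 | 0.77 |

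A t2 contrast with categorical time and a common baseline mean is unbiased in every row, with power 0.85. The shares hardly move with the error variance: across 1, 0.5 and 0.25 the plateau row stays at 0.72 and the halving row at 0.44 to 0.45. Power in those two rows does rise with smaller error variance (0.79, 0.86, 0.91 and 0.40, 0.46, 0.53).

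**Step 4, using baseline SIS.** Power at N = 558:

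| Error variance | Free-baseline slope, t0–t2 | Common baseline, t2 contrast |
|---|---|---|
| 1 | 0.799 | 0.850 |
| 0.5 | 0.904 | 0.911 |
| 0.25 | 0.969 | 0.969 |

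At error variance 1 the N for 80% power falls from 560 to 487, that is 73 fewer (13%).

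**The case against.** The strongest reply is that the text points towards a sound analysis. The sample size is for t2 and uses three time points, the t3 effect is a separate later analysis, and the t0-to-t3 trajectories are exploratory. On that reading the main model uses t0 to t2, where a linear fit misstates the t2 effect by at most about 4%. Coding of time and baseline adjustment are also details that an article can leave to an analysis plan that is not shown.

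Much of this stands. A reader might infer that the plan commits to a linear slope with a free baseline difference. The document does not say so: linearity is stated only for the sample-size model, baseline handling is stated nowhere, and the match to 558 needs an unstated error variance and is not unique. A reader might also infer that the trial is underpowered; it is not. A free-baseline model is valid, and the gain from using baseline ranges from about 5 points to none. Nor is there a fault in the three-level centre structure.

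What the reply does not remove is that the article itself states a primary time point, a test and a power model, and these do not target the same quantity. Reading the test as a t2 contrast, or as limited to t0 to t2, requires the reader to supply what the text leaves out.

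**Conclusion.** The point holds as a mismatch between endpoint and test: the t2 arm difference is the question, and it is not made the test. The consequence depends on the analysis eventually run. It is large only if a line is fitted to all four visits and the effect stops growing after t2: 0.18 SD under a plateau, 0.11 SD if the effect halves, against a true 0.25 SD. It is small if the model stops at t2, and it reverses in favour of the four-visit slope if growth is truly linear to month 12. The power figures rest on the assumed error variance of 1; the attenuation barely does. It should be fixed, with moderate confidence, and it is no reason to change the sample size.

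**What to change.** State in the analysis section that the primary test is the arm difference in SIS at t2. Take it from a mixed model with time as categories, arm-by-time terms, baseline SIS either constrained equal across arms or entered as a covariate, and site (the randomisation stratum) in the model. State which visits enter. Take the t1 and t3 differences from the same model as secondary contrasts.

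The cost is wording only, with no new patients or data. The downside is a few more parameters, and less power than a four-visit slope (0.85 against 0.97 at error variance 1) if the effect really does grow linearly to month 12.

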The peer support training has been manualised with a complementary workbook addressing underlying values and principles, specific skill training and preparing PSWs for tasks around recovery planning. The UPSIDES peer support training consists of 12 core modules: 1) understanding recovery and own recovery journey; 2) tree of life; 3) peer support; 4) communication; 5) recovery planning; 6) activating resources; 7) community and trialogue; 8) problem solving; 9) peer role description; 10) work preparation; 11) recovery groups; and 12) network. Training on local adaptations is provided via additional modules which consider context and address site-specific topics (social and environmental situation, resources in mental health care, stigma, rights and advocacy, trauma and disasters). An online training platform will facilitate exchange among trainers, PSWs and staff members at different study sites, helping to provide cross-site training and supervision while building an international PSW community.

UPSIDES peer support will be provided without hierarchy or judgement, taking into account principles of recovery-oriented care. UPSIDES PSWs will focus on: providing tangible supports; role modelling that recovery is possible; sharing personal experiences of mental health and ill-health; and promoting hope, and a sense of control and opportunities. Specific tasks include: initial assessment of strengths and resources to build on; practical support with daily life as needed (for example, accompaniment for appointments or activities); support during crises; and actively promoting recovery planning. Providing an additional recovery group setting is possible and recommended. UPSIDES peer support will be delivered for up to 6 months, with a minimum of three contacts. Weekly or biweekly meetings are recommended, but frequency may vary depending on the needs of service users, PSWs and study sites. The intervention manual provides additional materials to be used by the PSWs during the intervention. To support the implementation process, organisational readiness workshops are held across trial sites. Participants allocated to the control group (wait list) will start receiving the intervention after completion of follow-up (month 12). Criteria for discontinuing or modifying the intervention include change of content and dose of peer support or PSW in response to participant’s request, harms, or improving or worsening of illness.

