##### Allocation

Participants will be randomly assigned to either the control or intervention group with a 1:1 allocation as per a computer-generated randomisation schedule stratified by site using permuted blocks of random sizes. The block sizes will not be disclosed to ensure concealment. Participants will be randomised by an independent unit (Institute for Medical Biometry and Epidemiology, Ulm, Germany). All participants who give consent for participation and fulfil the inclusion criteria will be randomised. Allocation concealment will be ensured as the service will not release the randomisation code until the participant has been recruited into the trial and the baseline assessments completed.

Randomisation will be requested by the staff member responsible for recruitment and clinical interviews from the Institute for Medical Biometry and Epidemiology, Ulm, by e-mail. The randomisation form includes site ID, participant ID, gender of participant, date of informed consent and approval of eligibility. The requesting research worker will get a response by mail within one working day. For participants in the intervention group, the research worker will inform the local PSW team and the participant. Throughout the study, the randomisation will be conducted by the Institute for Medical Biometry and Epidemiology, Ulm, to keep the data management and the statistician blind to the study allocation for as long as the data bank is open. The randomisation list remains with the Institute for Medical Biometry and Epidemiology for the duration of the study. Randomisation will therefore be conducted without any influence of the principal investigators or raters.

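### The sample size makes no allowance for clustering by peer support worker in the intervention arm, so the stated power of 0.80 holds only if that correlation is zero

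*Protocol article*

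**What the plan says.** Under 'Statistical analysis and power calculation', the sample size is a completed calculation. The planned number "will be needed to detect a small effect size (0.25 SD units) with a power of 0.80 at a two-tailed significance level of 0.05". Its inputs are stated: "For six study sites, three time points, and estimated panel attrition of 10% at each time point", then "a person-level covariance (Int, Cov, Slope) of 0.300, 0.150, 0.100" and "a centre-level covariance (Int, Cov, Slope) of 0.050, 0.025, 0.020". The model is a "three-level mixed-effects linear regression model for the analysis of longitudinal data", so the levels are occasion, person and centre. No PSW level, PSW ICC or design effect appears.

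The analysis itself is described more loosely, as random-effect regression with a fixed group effect over time. Its random effects are not listed.

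Other sections describe delivery:

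- 'Intervention': a trained PSW delivers the support to one person or to a group. "Providing an additional recovery group setting is possible and recommended". A participant may ask to change PSW. Waiting-list controls start peer support only after month 12.
- Table 1: 279 service users (47 per site) and 60 PSWs (10 per site) are planned as raters of the process measures.
- 'Allocation': individual randomisation, "1:1 allocation as per a computer-generated randomisation schedule stratified by site using permuted blocks of random sizes". After allocation to the intervention, the local PSW team is informed.

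**The concern.** Participants supported by the same PSW share that worker's skill, style and availability, and some will also share a recovery group. Their outcomes are therefore likely to be correlated. This happens in one arm only, because controls have no PSW during follow-up.

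The centre-level terms do not cover it. Randomisation is stratified by site, so both arms share each centre effect and it largely cancels from the comparison. PSW effects do not cancel, because they exist in only one arm.

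Two things are at stake: whether N = 558 gives the power claimed for the primary outcome and, if the analysis also left PSW out, whether the 5% error rate would hold.

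**Working it through.** **Inputs from the article.** N = 558, so 279 per arm; 60 PSWs; effect 0.25 SD; two-sided alpha 0.05; power 0.80. I read 10% attrition at each time point as retention of 1, 0.9 and 0.81, so about 279 × 0.81 = 226 per arm at month 8.

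**Inputs assumed.** PSW ICC of 0.02, 0.05 or 0.10; one PSW per participant; equal caseloads; equal variance in the two arms.

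**Step 1: the plan's figure without PSW clustering.**

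- Closed form: n per arm = 2(1.960 + 0.842)² / 0.25² = 251.2, rounded up to 252, total 504. With a single 10% loss, 504/0.9 = 560, against 558 stated.
- From the stated covariances: the person-level variance at month 8 (time coded 0, 1, 2) is 0.300 + 4(0.150) + 4(0.100) = 1.3. The centre-level variance is 0.050 + 4(0.025) + 4(0.020) = 0.23. With an assumed residual variance of 1.0 the total is 2.53, and 0.25 SD is 0.25 × √2.53 = 0.398. The standard error of the linear-trend test at month 8 is about 0.142, so 0.398/0.142 = 2.80 and power is 0.80.

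Both are reconstructions. The residual variance and the SD to which the 0.25 refers are not stated, and other choices give other powers. What matters is that 0.80 can be reached with no PSW term at all. The next steps start from the plan's own 0.80.

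**Step 2: caseload.** At randomisation m = 279/60 = 4.65. Retained at month 8, m = 226/60 = 3.77.

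**Step 3: effect of partial nesting.**

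- Intervention-arm design effect: DE = 1 + (m − 1) × ICC
- Variance ratio of the group contrast, with one arm of two inflated: VR = (1 + DE)/2
- Power = Φ(2.802/√VR − 1.960)
- Type I error if PSW is ignored = 2[1 − Φ(1.960/√VR)]

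| ICC (assumed) | m | DE | VR | SE ratio √VR | Power | Type I error if PSW is ignored |
|---|---|---|---|---|---|---|
| 0.02 | 4.65 | 1.073 | 1.036 | 1.018 | 0.786 | 5.4% |
| 0.02 | 3.77 | 1.055 | 1.028 | 1.014 | 0.789 | 5.3% |
| 0.05 | 4.65 | 1.183 | 1.091 | 1.045 | 0.765 | 6.1% |
| 0.05 | 3.77 | 1.138 | 1.069 | 1.034 | 0.773 | 5.8% |
| 0.10 | 4.65 | 1.365 | 1.183 | 1.087 | 0.731 | 7.1% |
| 0.10 | 3.77 | 1.277 | 1.138 | 1.067 | 0.747 | 6.6% |

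**Step 4: cross-check from the covariances.** With the assumed residual variance of 1.0, the within-centre variance at month 8 is 1.3 + 1.0 = 2.3. At ICC 0.05 the added variance is 0.05 × 2.3 × (1/60 − 1/226) = 0.0014. Against 0.142² = 0.0202 this is 7%, an SE ratio of 1.034. It agrees with the row for m = 3.77.

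**Step 5: what the loss is worth.** At caseload 4.65, the N that restores 0.80 is 558 × VR, about 578, 609 and 660. At N = 558, the effect detectable with power 0.80 is 0.25 × √VR. This is 0.253 to 0.255 SD at ICC 0.02, 0.259 to 0.261 at 0.05, and 0.267 to 0.272 at 0.10.

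**Step 6: sensitivity.** With uneven caseloads (assumed coefficient of variation 0.5, m = 4.65), power is 0.754 at ICC 0.05 and 0.711 at 0.10. 'Limitations' expects attrition among peer staff. If, as an assumption, 40 PSWs carried the 226 (m = 5.65), power would be 0.755 and 0.713. Recovery groups would add correlation, but their size and composition are not given, so I do not quantify them.

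**The case against.** The strongest objection concerns the analysis. A reader might infer that the analysis model leaves PSW out, so that its standard errors are certainly too small. The article does not support that. The three-level wording belongs to the sample size calculation, the analysis sentence lists no random effects, and a condensed article may leave them to an analysis plan that is not shown. This objection stands: the type I error figures are conditional.

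Second, no ICC is given. With a small caseload and only one nested arm, the loss is under 2 points at ICC 0.02 and passes 2 points only at roughly 0.03 (m = 4.65: power 0.779). This stands as to size. It does not change the direction: leaving the term out amounts to assuming an ICC of exactly zero.

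Third, 60 and 279 are planned rater numbers, so the caseload is inferred. Participants may change PSW, and only a PSW team is said to be informed, so nesting is imperfect. This also stands in part. But these are the only PSW numbers in the document, 279 is exactly half of 558, and imperfect nesting weakens clustering without removing it.

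The objection that the analysis plan may settle the matter does not reach the sample size. N was fixed without the allowance. Adding a PSW term later protects the error rate but cannot restore the power.

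**Conclusion.** The point holds for the sample size. The stated power of 0.80 is an upper bound, reached only if outcomes are uncorrelated within PSW. For assumed ICCs of 0.02, 0.05 and 0.10, power at N = 558 is about 0.79, 0.77 and 0.73 to 0.75; the last range reflects whether caseload is counted at randomisation or at month 8. If the analysis also used only three levels, type I error would be about 5.3%, 6% and 7%.

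These figures rest on an assumed ICC and an inferred caseload, and the cross-check rests on an assumed residual variance of 1.0. It would go too far to say that the trial is seriously underpowered or that its primary test is invalid. The loss is a few points over most of the range, and the analysis model is not specified closely enough to be called wrong. This should be fixed, but it is not critical.

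**What to change.** - Record the first-assigned PSW for every intervention participant, prospectively, at the point where the local PSW team is informed. Reconstructing it after staff turnover would be unreliable. Using the first assignment keeps the grouping in line with intention to treat.
- State in the primary analysis that a PSW random effect acts in the intervention arm only (a partially nested model).
- Keep N = 558 if it cannot change, but restate its power, or the detectable effect, over a declared range of PSW ICC and caseload. State the residual variance used in the sample size program so that the calculation can be repeated.

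The cost is one identifier per intervention participant, a short change to the analysis text, and a slightly lower stated power. The nesting will be approximate where participants change PSW or see several, and the report should say so.

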### Cost-effectiveness analysis

#### Measures

Comprehensive societal costs of mental illness will be estimated for each participating country using an adapted version of the Client Sociodemographic and Service Receipt Inventory (CSSRI) [37] at t_0_ to t_3_. The CSSRI-UPSIDES will be adapted for use at all sites to assess mental health service use and productivity losses due to mental illness. If not already available, country-specific unit costs of health and social care services will be determined by investigating publicly accessible sources (price lists, catalogues of fees and charges), by expert interviews or by calculations of staff and capital costs for services used, drawing on the principles recently developed by the Global Health Cost Consortium in their reference case for global health costing [38]. All costs will be converted into USD ($) using purchasing power parities [39]. Quality-adjusted life years (QALYs) will be estimated using the EQ-5D 3 L at t_0_ to t_3_ as used in most multinational cost-utility studies [40] and being available in the languages of all study sites. As country-specific population-based value sets are not available for most study sites, QALYs will be estimated on the basis of the European EQ-5D visual analogue scale for all countries [41].

